## 2. Materials and Methods

### 2.1. Study Design

This is a cross-sectional, vignette-based experiment with a four-level within-subjects (repeated-measures) design. Vignette experiments combine the internal validity of experimental manipulation with survey feasibility and are an established method for isolating drivers of health-related judgments [61]; their design and analysis follow current methodological guidance for vignette data [62]. Each participant reads and evaluates all four scenarios of AI implementation (A–D), presented in a counterbalanced sequence. The within-subjects structure makes each respondent their own control, eliminating inter-individual variability from between-scenario comparisons and substantially increasing statistical power relative to a between-subjects design of the same size [63]. The presentation sequence is counterbalanced. The survey platform allocates participants at random, in equal proportions and independently of any participant characteristic, to one of the four sequences of a Williams (balanced Latin-square) design: A → B → C → D, B → D → A → C, C → A → D → B, and D → C → B → A. In this square, every scenario occupies every serial position exactly once, and every ordered pair of scenarios occurs exactly once, so that autonomy level is orthogonal both to serial position and to first-order carry-over, and an additive model containing a four-level autonomy effect and a four-level serial-position effect is fully identified. The theoretically motivated ascending sequence and its exact mirror image are retained as two of the four arms. A fixed ascending presentation would have mirrored the progressive continuum under investigation and given every participant an identical evaluation context, but it would have left order, carry-over, and fatigue effects inseparable from the autonomy gradient; because H1–H3 concern precisely that gradient, internal validity was given priority over uniformity of context. Counterbalancing also makes the embedded manipulation check diagnostic rather than merely descriptive: perceived AI control should track the described autonomy level within every sequence, whereas an anchoring or fatigue artifact would instead track serial position—a distinction that a monotonic manipulation-check profile obtained under a fixed order cannot draw. Presentation sequence is therefore retained as a between-subjects factor in all primary models, a second manipulation check (perceived technical sophistication) separates autonomy from technical complexity, and a per-scenario difficulty item indexes fatigue (Section 2.6, Section 2.7, Section 2.8, and Section 2.9.1). The study involves no medical, pharmacological, or surgical intervention. Reporting of the completed study will follow current recommendations for effect-size-based reporting [64] and, for the web-survey component, the CHERRIES checklist as operationalized in recent methodological guidance [65]. Publication of the protocol in advance of data collection is intended to reduce publication bias and analytic flexibility [66,67].

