The per-scenario response block contains nine Likert items measuring the three primary dependent variables—acceptability (ACC1–ACC3), trust (TRU1–TRU3), and perceived risk (RSK1–RSK3)—followed by six responsibility items (RES1–RES4: surgeon, hospital, AI developer, unavoidable medical uncertainty; RES5: the surgeon’s moral duty to verify AI outputs; RES6: outcome-independent accountability), two manipulation-check items (MAN1: perceived AI control over the final surgical decision; MAN2: perceived technical sophistication of the system), and a perceived difficulty item (DIF1). All scaled items use 7-point end-anchored Likert response formats. Composite scores are computed as the arithmetic mean of their items after reverse-scoring RSK1 (8 − score), which is the only reverse-keyed item in the response block; higher risk scores indicate higher perceived risk. Treating item means on end-anchored 7-point scales as quasi-continuous interval variables is standard practice in experimental vignette research; ordinal-model sensitivity analyses are nevertheless planned in line with current guidance on Likert-based outcomes [62,71]. Table 4 summarizes the measurement structure; per-scenario variables carry the scenario suffix (e.g., ACC1_A, ACC1_B, ACC1_C, ACC1_D).

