
### 2.8. Pilot Study and Instrument Validation

The instrument will be validated in a pilot study (*N* = 50, not included in the main sample, allocated 1:1 to the ascending sequence A → B → C → D and to its exact reverse D → C → B → A) before the main study is launched. The pilot will estimate (i) internal consistency—Cronbach’s α and McDonald’s ω with 95% confidence intervals for each three-item composite, computed separately per scenario, against a threshold of ≥0.70, with ω reported alongside α in line with current psychometric guidance [73]; with three items per construct, α ≥ 0.70 requires a mean inter-item correlation of only $\bar{r}$ ≥ 0.44 under the generalized Spearman–Brown relation (Figure 2), a realistic requirement for parallel items; (ii) inter-item correlations (flagged at r > 0.90 for redundancy or r < 0.20 for heterogeneity) and corrected item-total correlations (threshold ≥ 0.40), plus the correlation between repeated measurements, reported with a 95% confidence interval, to verify the ρ ≈ 0.50 planning assumption and, where it is not met, to trigger the adaptive sample-size rule of Section 2.5; (iii) the factor structure of the nine response items, via exploratory factor analysis (principal-axis extraction, oblique rotation, sampling adequacy KMO ≥ 0.70, Bartlett’s test of sphericity, parallel analysis as the retention criterion)—an anticipated risk is that acceptability and trust items form a single factor, in which case the two constructs will be merged into a single “trust–acceptance” score and the analysis plan adjusted transparently before pre-registration, with this decision taken exclusively on pilot data; (iv) first-attempt comprehension-check pass rates per scenario (threshold ≥ 70%); (v) manipulation validity—MAN1 scores must order the scenarios from A to D in both pilot arms, while MAN2 (perceived technical sophistication) must not increase monotonically with autonomy; if it does, the vignettes will be reworded to equalize the described sophistication of the systems and the check repeated before pre-registration; (vi) fatigue—perceived difficulty (DIF1) and section-wise drop-out across serial positions in both arms; (vii) cognitive interviews with 5–8 participants to identify confusing wording, probing in particular whether RES1–RES6 are read in the intended senses of moral answerability, outcome-independent accountability, and legal fault (Section 2.6); and (viii) a first bound on order effects—the two pilot arms are compared on the three composites and on MAN1 by a scenario × order mixed ANOVA (*n* = 25 per arm; minimum detectable interaction *f* = 0.17 at ρ = 0.50), which can exclude medium-to-large order artifacts but not small ones, the definitive test being the main-study interaction. The four-sequence randomizer used in the main study is implemented in the same pilot build. Because the pilot itself exercises only two of the four arms, the randomizer is verified there by simulated allocation, which also confirms that the allocated sequence and the serial position of each scenario are stored correctly. A ninth objective is included: (ix) the keying and dimensionality of the four general-attitude items (G1–G4), since G3 is a caution item that the present scoring treats as positively keyed while G2 and G4 are reversed; the scoring rule for that block is fixed on pilot data before pre-registration, and if the four items do not form a single interpretable dimension they will enter the person-level analyses individually rather than as a composite. Because a sample of 50 is at the lower limit for stable factor solutions, the pilot EFA is treated as provisional: the factor structure will be re-examined by confirmatory factor analysis on the main sample (*N* = 300), with acceptable fit defined a priori as CFI/TLI ≥ 0.95, RMSEA ≤ 0.06, and SRMR ≤ 0.08. Because the same nine items are answered four times, longitudinal measurement invariance across the four scenario repetitions (configural, metric, and scalar) will also be tested on the main sample; at least partial scalar invariance is required for the between-scenario comparison of composite means, and any non-invariant item will be reported and handled by partial-invariance modeling. Pilot results will be reported in the methods section of the results article.

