
### 2.9. Statistical Analysis

#### 2.9.1. Primary Analyses

Each composite score (acceptability, trust, perceived risk) will be analyzed by a mixed repeated-measures ANOVA, with autonomy level (four scenarios) as the within-subjects factor and presentation sequence (four Williams sequences) as the between-subjects factor. The Greenhouse–Geisser correction will be applied when Mauchly’s test indicates a sphericity violation (Huynh–Feldt for ε between 0.75 and 1), and the multivariate approach (Pillai’s criterion) will be reported in parallel as a sphericity-robust check. H1 and H2 will be tested with within-subjects trend contrasts across the autonomy gradient. Because acceptance need not fall in a straight line, the complete set of orthogonal polynomial contrasts—linear, quadratic, and cubic—is pre-specified, and each is reported together with the proportion of the omnibus effect it accounts for. A purely linear profile leaves the quadratic and cubic components negligible, whereas a step between two adjacent levels appears as a large linear component accompanied by a substantial quadratic or cubic one. Because every monotone step is linear-dominant, the polynomial decomposition establishes departure from a straight line but cannot by itself locate the break; the break is identified only from the Holm-corrected adjacent-pair contrasts (A–B, B–C, C–D). A quadratic-dominant profile with a small linear component would instead indicate a non-monotone pattern, which the hypotheses do not predict and which would be reported as such. A non-monotonic or threshold pattern will be reported as such rather than summarized by the linear trend alone. Post hoc comparisons use dependent-samples *t*-tests for the six scenario pairs with Holm’s sequential correction, applied within each hypothesis-defined family of tests in line with current guidance on multiplicity control [74]. Effect sizes will be reported as partial η^2^ for omnibus tests and Cohen’s dz for pairwise comparisons, with 95% confidence intervals, following effect-size-centered reporting recommendations [64]. Assumption checks include graphical inspection of difference-score distributions; as a distributional robustness analysis, the Friedman test with Holm-corrected Wilcoxon signed-rank pairwise comparisons will be reported alongside each primary test—supplemented by ordinal (cumulative-link) models as sensitivity analyses for the Likert-based outcomes [71]—and the concordance of parametric and nonparametric conclusions stated explicitly. Order dependence is tested directly as the scenario × sequence interaction; a non-significant interaction, together with equivalence of the four sequence-specific profiles, supports pooling across sequences. Independently of that test, the autonomy effect is re-estimated from a linear mixed model with random intercepts per participant and additive fixed effects of autonomy level and serial position (1–4). The Williams square renders this model identified, so the estimate is adjusted for arbitrary—not merely linear—serial-position and fatigue effects, while first-order carry-over is balanced by the design rather than modeled; position-adjusted and unadjusted estimates are reported side by side, and any material divergence between them is treated as evidence of an order artifact and interpreted accordingly. Perceived difficulty (DIF1) and perceived technical sophistication (MAN2) are each added as time-varying covariates in further sensitivity models, addressing fatigue and the possibility that responses track the apparent complexity of the system rather than its autonomy. Finally, between-person heterogeneity in response profiles is examined by adding a random slope for the linear autonomy contrast and testing the improvement in fit by a likelihood-ratio test; a substantial random-slope variance indicates that an average trajectory conceals distinct response patterns and licenses the exploratory typology described in Section 2.9.2. Because a non-significant test is not evidence of absence, a smallest effect size of interest of *dz* = 0.20—the value detectable at the Bonferroni bound for the six pairwise contrasts at *N* = 300—is fixed in advance, and equivalence testing by two one-sided tests against that bound is reported alongside every null pairwise result, so that any claim that two adjacent scenarios do not differ rests on an equivalence test rather than on the absence of significance.

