Several limitations are accepted by design and will be declared in the results article. First, the sample is a self-selected online convenience sample: results describe Romanian adults active in digital environments—likely younger and more educated than the general population—and do not support national generalization; the sample structure will be reported against National Institute of Statistics reference data. Second, the vignettes are hypothetical, and the distance between a vignette judgment and a decision taken in a consulting room is not merely one of degree. Participants evaluate a scenario in which they are not injured, not in pain, not facing a scheduled operation, and not choosing between real surgeons. They bear no consequences for the judgment they record, receive no counseling, and cannot ask questions. Above all, they are not exposed to the most influential element of real surgical decision-making: a conversation with the clinician who would operate, whose endorsement and explanation are known to shift acceptance of AI-supported care substantially [27,28]. Stated acceptability under these conditions is best read as a measure of prior disposition toward a described scenario rather than as a prediction of consent behavior. The ordering of the scenarios is likely to be more robust than the absolute levels, which could be lower than those a counseled patient would report or higher if hypothetical risk is discounted. This is a standard limitation of vignette methodology [61,62], and the remedies lie outside the present design: replication among patients actually scheduled for facial reconstructive surgery, and ultimately observation of consent decisions where such systems are in use. Third, presentation sequence is counterbalanced but not thereby rendered irrelevant. The Williams square balances serial position and first-order carry-over, so that the autonomy effect is estimable free of both, but no four-sequence design balances higher-order carry-over—a participant’s evaluation of the third scenario being shaped jointly by the first two—and contrast effects that depend on which scenario was seen immediately before therefore remain possible. The scenario × sequence interaction, the position-adjusted model, and the difficulty covariate bound the magnitude of what remains; they do not remove it, and a large residual would warrant a between-subjects replication in which each participant evaluates a single scenario. Fourth, demand and contrast effects are inherent to within-subjects designs: seeing all scenarios, participants may infer the study objective and exaggerate differentiation between scenarios; comparisons remain internally valid, but absolute difference magnitudes warrant caution. Fifth, all measures share a common method and a single measurement occasion, in a rapidly evolving attitude domain [38]. Sixth, the survey platform does not record completion time, so quality control relies on embedded checks rather than temporal filters [69]. Seventh, the demographic and familiarity subgroups formed within a convenience sample of 300 will differ substantially in size, and several will be small; the minimum-cell rule of Section 2.9.2, and the requirement that subgroup differences be inferred only from formal interaction terms, are intended to forestall the familiar error of asserting a difference from a significant effect in the larger subgroup together with a non-significant one in the smaller. None of these limitations is unusual for online vignette experiments, and declaring them in advance is intended to keep the eventual findings interpretable at their proper scope.

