Scenario × sequence interaction—order test (*df* = 9)	*N* = 300, ρ = 0.50	*f* = 0.08
Scenario × sequence interaction—order test (*df* = 9)	*N* = 300, ρ = 0.30	*f* = 0.10
Pilot order bound, ascending vs. descending arm (*df* = 3)	*N* = 50, ρ = 0.50	*f* = 0.17
Dependent comparison within a demographic subgroup	*n* = 50, α = 0.05	*dz* = 0.40

Abbreviations: RM-ANOVA, repeated-measures analysis of variance; *N*, number of valid participants; *n*, number of participants per pilot arm or subgroup; ρ, correlation between repeated measurements; α, significance threshold; *df*, degrees of freedom; f and *f*^2^, Cohen’s effect-size indices for *F* tests; *dz*, Cohen’s effect size for dependent-samples comparisons; *w*, effect size for the goodness-of-fit chi-square test.

**Table 3 healthcare-14-03030-t003:** Projected recruitment funnel.

Stage	Assumed Pass Rate	Estimated Number
Link accesses	—	≈545
Begin questionnaire (consent given)	85% of accesses	≈463
Eligible after screening (items S1, S2)	96% of starters	≈445
Completed (submitted) questionnaires	75% of eligible	≈334
Valid after quality exclusions (ATT, CC, invariant, duplicates)	90% of submitted	≈300

Abbreviations: S1 and S2, the two screening items of the instrument (Appendix A.1); ATT1 and ATT2, attention checks; CC_A–CC_D, comprehension checks.

**Table 4 healthcare-14-03030-t004:** Measurement structure of the instrument.

Construct/Variable	Items	Scale	Role in Analysis
Acceptability	ACC1–ACC3 (mean), per scenario (×4)	Likert 1–7	Primary DV (H1), within-subjects
Trust	TRU1–TRU3 (mean), per scenario (×4)	Likert 1–7	Primary DV (H1), within-subjects
Perceived risk	RSK1 (reversed), RSK2, RSK3 (mean), per scenario (×4)	Likert 1–7	Primary DV (H2), within-subjects
Responsibility attribution	RES1–RES4, per scenario (×4)	Likert 1–7	Secondary DV (H3), within-subjects
Responsibility principles	RES5, RES6, per scenario (×4)	Likert 1–7	Secondary DV
Global preference	P1	7 response options (6 analysis categories)	Secondary DV
General acceptability	P3	Likert 1–7	Secondary DV
AI familiarity	B1	Likert 1–7	Moderator (H4)/covariate
General AI attitudes	G1–G4 (G2, G4 reversed)	Likert 1–7	Covariates
Experience and demographics	B2–B5, D1–D7	Mixed	Covariates/sample description
Manipulation check (perceived AI control)	MAN1, per scenario (×4)	Likert 1–7	Design validation
Scenario difficulty	DIF1, per scenario (×4)	Likert 1–7	Control covariate (fatigue)
Data quality	ATT1, ATT2, CC_A–CC_D	Categorical	Exclusion criteria

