Trust in the healthcare system	B6	Likert 1–7	Covariate/exploratory moderator
Manipulation check (technical sophistication)	MAN2, per scenario (×4)	Likert 1–7	Design validation/covariate
Presentation sequence	SEQ	4 categories	Between-subjects design factor
Serial position of scenario	POS	1–4	Covariate (order, fatigue)

Abbreviations: DV, dependent variable; ACC, acceptability items; TRU, trust items; RSK, perceived-risk items; RES, responsibility items; MAN1 and MAN2, manipulation-check items; DIF1, perceived-difficulty item; ATT1 and ATT2, attention checks; CC_A–CC_D, comprehension checks; B1–B6, background items; G1–G4, general-attitude items; P1–P4b, preference items; D1–D7, demographic items; SEQ, presentation sequence; POS, serial position of the scenario; H1–H4, hypotheses 1–4.

**Table 5 healthcare-14-03030-t005:** Hypothesis-by-hypothesis analysis plan.

Hypothesis/Objective	Planned Test	Reported Coefficients
Manipulation validation	Mixed RM-ANOVA on MAN1 (autonomy within × sequence between) + polynomial trend contrasts; the intended ordering A → D expected within every sequence	*F*, corrected *df*, *p*, partial η^2^; ε(GG)
H1. acceptability and trust decline with autonomy	Mixed RM-ANOVA per composite, sequence as between-subjects factor (Greenhouse–Geisser) + orthogonal polynomial trend contrasts (linear, quadratic, cubic); post hoc dependent *t*-tests, Holm correction	*F*, corrected *df*, *p*, partial η^2^ (90% CI); pairwise dz (95% CI)
H2. perceived risk increases with autonomy	Mixed RM-ANOVA (autonomy within × sequence between) + orthogonal polynomial trend contrasts; post hoc dependent *t*-tests, Holm correction	*F*, corrected *df*, *p*, partial η^2^; pairwise *dz*
H3. responsibility migrates surgeon → AI developer	4 × 4 mixed ANOVA (scenario × actor within, sequence between), Greenhouse–Geisser; the scenario × actor interaction is the test of H3; repeated with a serial-position term	*F*, corrected *df*, *p*, partial η^2^; ε(GG)
Responsibility concentration	Normalized Herfindahl–Hirschman index (RES1–RES3) per scenario, compared by mixed RM-ANOVA (sequence between)	Mean HHI per scenario; *F*, *p*, partial η^2^
Moral–legal distinction	Mixed RM-ANOVAs on RES5 and RES6 across scenarios (sequence between); Holm correction within family	*F*, corrected *df*, adjusted *p*, partial η^2^

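### Adding DIF1 as a covariate cannot correct fatigue in the autonomy contrasts or bound residual order effects; DIF1 should be analysed as an outcome by serial position

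*Protocol article*

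**What the plan says.** Section 2.6 lists, after each vignette's outcome items, two manipulation checks "and a perceived difficulty item (DIF1"). The item wording is not shown.

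The article gives this rating a fatigue role in four places:
- Section 2.1: "a per-scenario difficulty item indexes fatigue".
- Table 4: the row is headed scenario difficulty, but the role reads "Control covariate (fatigue").
- Section 2.9.1: DIF1 and MAN2 "are each added as time-varying covariates in further sensitivity models, addressing fatigue and the possibility that responses track the apparent complexity" of the system.
- Section 4, third limitation: besides the scenario × sequence interaction, "the position-adjusted model, and the difficulty covariate bound the magnitude of what remains" after counterbalancing.

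Three other statements bear on this. Section 2.1 says that "autonomy level is orthogonal both to serial position and to first-order carry-over". Table 4 has a separate serial-position variable with the role "Covariate (order, fatigue"), and Section 2.9.1 fits a mixed model with it. Section 2.8 uses DIF1 differently in the pilot: "fatigue—perceived difficulty (DIF1) and section-wise drop-out across serial positions in both arms". For the main study, the only analysis of DIF1 that the article states is as a covariate; Table 5 has no row for it.

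**The concern.** A covariate can remove fatigue bias from the autonomy contrasts only if such bias is there and the covariate carries it. The design already balances serial position across scenarios, so additive fatigue does not enter those contrasts. What remains in DIF1 at the level of scenario means is how hard each vignette was found, which is a response to the manipulation. Conditioning on it changes the estimand from the total effect of scenario to an effect at equal rated difficulty.

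The risk is one of interpretation. A smaller gradient after DIF1 adjustment could be put down to fatigue when it reflects scenario difficulty. An unchanged gradient could be offered as evidence against fatigue although the model could not have shown otherwise. The Discussion would also credit the study with a bound on residual order effects that this covariate does not supply.

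**Working it through.** **The plan's own figures.** The article gives no figure for DIF1. Its planning figures reproduce and are not in dispute. With λ = f² × N × 4/(1 − ρ) and df = 3 and 3(N − 1), f = 0.10 and ρ = 0.50 require N = 138, as stated (λ = 0.01 × 138 × 4/0.5 = 11.04).

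**Step 1: balance.** Serial positions of each scenario over the four sequences in Section 2.1 (ABCD, BDAC, CADB, DCBA):
- A: 1, 3, 2, 4
- B: 2, 1, 4, 3
- C: 3, 4, 1, 2
- D: 4, 2, 3, 1

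Each scenario takes each position once, and all 12 ordered adjacent pairs occur once.

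**Step 2: algebra.** Let mean DIF1 for scenario s at position p be m + d(s) + t(p), and the mean outcome be a(s) + g(p). With equal sequences, every scenario mean contains the same average of t and the same average of g. Therefore:
- unadjusted contrast i − k = a(i) − a(k), with no fatigue term;
- difference in mean DIF1 = d(i) − d(k), with no fatigue term;
- adjusted minus unadjusted contrast = −b × [d(i) − d(k)], where b is the within-person slope of the outcome on DIF1.

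Additive fatigue appears nowhere in the shift. Its sign depends on b and on which scenario is rated harder; it is zero if mean DIF1 does not differ.

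**Step 3: simulation.** N = 300, equal sequences, 1000 runs, within-person regression of the outcome on scenario, with and without DIF1. All effect sizes are assumptions. D − A contrast:

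| Setting | Without DIF1 | With DIF1 |
|---|---|---|
| DIF1 driven by fatigue only; fatigue also lowers the outcome | −1.00 | −1.00 |
| D rated 0.6 harder than A, b = −0.4 | −1.24 | −1.00 |
| D rated 0.6 easier than A, b = −0.4 | −0.76 | −1.00 |
| DIF1 has no effect on the outcome but shares a cause; D harder | −1.00 | −0.80 |
| Same, D easier | −1.00 | −1.20 |
| Same, D harder, true contrast zero | 0.00 | +0.19 |
| Effect of fatigue on the outcome is larger in D | −1.30 | −1.30 |

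Rows 2 and 3 agree with the formula: −(−0.4) × 0.6 = +0.24 and −(−0.4) × (−0.6) = −0.24. In the last row the true contrast without fatigue is −1.00. The distortion of −0.30, of a kind that balancing does not remove, passes through the DIF1-adjusted model untouched, so the model neither removes nor bounds it.

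**Step 4: the Discussion's claim.** What the third limitation says remains is higher-order carry-over, and contrast effects that depend on the preceding scenario. A difficulty rating of the current vignette does not record that history, and Step 2 shows that the DIF1-adjusted contrast differs from the unadjusted one only through scenario differences in rated difficulty.

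**Step 5: the alternative.** A separate simulation (75 per sequence, 60 replicates) fitted DIF1 on scenario + serial position. It estimated the position 4 minus position 1 effect at 1.49 when the assumed value was 1.5, and at 0.00 when there was none.

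**The case against.** Four points can fairly be made for the plan.

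- **DIF1 can index fatigue.** This stands. Averaged by serial position in a balanced design, it is a legitimate indicator, and the pilot uses it that way. A reader might infer that DIF1 does not measure fatigue at all. The documents do not support that: the item wording is not shown, and Step 5 shows that a position effect is recoverable.
- **The covariate may do no harm.** This stands in part. Section 2.2 says the vignettes are matched on length, reading difficulty and amount of technical detail; if that succeeds, DIF1 differences and the shift may be small. Returning the same contrast under additive fatigue is also the right answer. If DIF1 carries the fatigue, the covariate can absorb position variance: in one simulated case the standard error fell from 0.069 to 0.057. That is a gain in precision, not a correction of bias.
- **Fatigue control does not rest on this model.** This stands. The scenario × sequence test, the serial-position mixed model and drop-out by position do that work.
- **No stated rule reads a DIF1 shift as an order artifact.** Correct: the divergence rule in Section 2.9.1 concerns position-adjusted against unadjusted estimates. But the article does label the covariate a fatigue control and counts it as a bound, which invites that reading.

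A reader might also infer that the adjustment can only strip out part of the true autonomy effect. It cannot be put so strongly: Step 3 shows it shrinking, enlarging, creating or leaving a contrast unchanged.

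**Conclusion.** The concern holds in a limited form and is minor. As a time-varying covariate, DIF1 has no additive fatigue bias to correct in the autonomy contrasts. It moves them only through between-scenario differences in mean DIF1, in either direction or not at all. Neither outcome is evidence about fatigue, and the statement in Section 4 that the covariate helps bound residual order effects is unsupported.

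The size is −b × (difference in mean DIF1). The documents give neither term, so every magnitude above is illustrative: 0 with no difference in DIF1, ±0.24 points with b = −0.4 and a difference of ±0.6. The cancellation assumes equal numbers per sequence and additive fatigue. If completers are unequal across sequences, exact orthogonality is lost, but the remedy is the serial-position model already planned, not DIF1. No primary test, confirmatory estimate or sample size changes.

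**What to change.** - **Section 2.9.1:** analyse DIF1 in the main study as an outcome, in a model with scenario and serial position (1–4). Report the position effect as the fatigue indicator and the scenario effect as a difference in difficulty. Keep the serial-position model as the fatigue adjustment for the autonomy effect.
- **If a DIF1-adjusted autonomy model is kept:** label it exploratory, state that it conditions on a rating made after the vignette, and do not call it a fatigue control.
- **Section 4, third limitation:** delete the difficulty covariate from the list of bounds.
- **Table 4:** change the role of DIF1 to outcome (fatigue/difficulty check).

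The cost is wording before pre-registration and one swapped model on data that will be collected anyway. The downside is one fewer adjusted sensitivity estimate and, if DIF1 does carry fatigue, the loss of that model's possible small gain in precision.
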